## Abstract

**Background:**

Early accurate assessment of burn depth is important to determine the optimal treatment of burns. The method most used to determine burn depth is clinical assessment, which is the least expensive, but not the most accurate.

Laser Doppler imaging (LDI) is a technique with which a more accurate (>95%) estimate of burn depth can be made by measuring the dermal perfusion. The actual effect on therapeutic decisions, clinical outcomes and the costs of the introduction of this device, however, are unknown. Before we decide to implement LDI in Dutch burn care, a study on the effectiveness and cost-effectiveness of LDI is necessary.

**Methods/design:**

A multicenter randomised controlled trial will be conducted in the Dutch burn centres: Beverwijk, Groningen and Rotterdam. All patients treated as outpatient or admitted to a burn centre within 5 days post burn, with burns of indeterminate depth (burns not obviously superficial or full thickness) and a total body surface area burned of ≤ 20% are eligible. A total of 200 patients will be included. Burn depth will be diagnosed by both clinical assessment and laser Doppler imaging between 2–5 days post burn in all patients. Subsequently, patients are randomly divided in two groups: ‘new diagnostic strategy’ versus ‘current diagnostic strategy’. The results of the LDI-scan will only be provided to the treating clinician in the ‘new diagnostic strategy’ group. The main endpoint is the effect of LDI on wound healing time.

In addition we measure: a) the effect of LDI on other patient outcomes (quality of life, scar quality), b) the effect of LDI on diagnostic and therapeutic decisions, and c) the effect of LDI on total (medical and non-medical) costs and cost-effectiveness.

**Discussion:**

This trial will contribute to our current knowledge on the use of LDI in burn care and will provide evidence on its cost-effectiveness.

**Trial registration:**

NCT01489540

## Background

In patients with burns an early accurate diagnosis of burn depth is essential to determine the most appropriate treatment. Monstrey et al. recently reviewed all current modalities to diagnose burn depth. Bedside clinical examination is the most widely used and least expensive method for burn depth assessment. This technique is effective when diagnosing burns at the extreme end of the spectrum: superficial or full thickness. In partial thickness burns, however, clinical examination is not very accurate. Clinical burn depth assessment is accurate in about 2/3 of the cases, the most reported error is overestimation of depth [1].

Overestimation of burn depth can lead to unnecessary excision and grafting [2,3]. On the other hand, underestimation of burn depth may lead to an unnecessary delay in surgery, with a longer length of hospital stay and higher hospital costs as a consequence [4,5]. In burn care, traditionally classified as expensive care, there is a growing interest in costs and cost control [6,7]. In order to provide effective and cost-effective burn care, there is a need for an accurate method for burn depth estimation.

Laser Doppler imaging (LDI) is the only technique that has been shown to accurately predict wound depth with a large weight of evidence [1]. Laser Doppler imaging is based on the Doppler principle. Laser light that is directed at moving blood cells in sampled tissue exhibits a frequency change that is proportional to the amount of perfusion in the tissue. Laser Doppler imaging combines the advantages of laser Doppler and scanning techniques: the whole burn can be sampled and no direct contact with the burn surface is necessary [2]. In daily practice, LDI will be used in combination with standard clinical assessment [8], as a so-called add-on test [9].

Several prospective studies on the diagnostic accuracy of laser Doppler imaging have demonstrated an accuracy varying between 95-100% [3,8,10-12]. Timing of LDI is important: only scanning between 48 hours and 5 days results in a high accuracy (>95%) [8,11,13,14].

To decide whether a new diagnostic strategy, like LDI, should be implemented, assessment of diagnostic accuracy should be followed by assessment of diagnostic and therapeutic impact, effectiveness and cost-effectiveness of the new technology [9,15].

The literature on the accuracy of LDI in burn depth assessment is convincing. However, most studies only report on the accuracy of this technique. The diagnostic and therapeutic impact of the introduction of LDI is often only speculated upon.

There is, to our knowledge, only one retrospective cohort study [4], and one prospective non-randomized study [5] that investigated the therapeutic impact of the introduction of laser Doppler imaging. Petrie et al. reported a lower rate of operative interventions (6.8% before and 2.2% after, p= 0.029) in a pediatric burn population after the introduction of LDI and a reduced length of hospital stay of the surgical treated patients (15.1 days before and 9.8 days after, no p-value). The overall length of stay was 3.4 days in 235 patients before and 2.1 days in 270 patients after the introduction of the LDI [4]. Because of the retrospective nature of this study, other factors than the introduction of LDI alone could be responsible for the therapeutic changes [9]. In the study of Kim et al. [5] the impact of LDI on surgically treated pediatric patients with burns was investigated. The mean time to decision making for grafting procedures was shorter in the LDI group compared to the clinically assessed group (8.9 vs. 11.6 days, p= 0.01). Because of the non-randomised design, it is unclear whether this can be contributed to the LDI or to other differences between the groups.

Thus, current research gives some indications on the diagnostic and therapeutic impact of the LDI in burm care. However, randomised studies in both pediatric and adult patients with burns are lacking.

The introduction of LDI possibly leads to a cost reduction in burn care, by preventing unnecessary surgery [3,4], and reducing length of hospital stay [4]. However, no prospective studies are available on the costs and the possible cost reduction of LDI in burn care, nor are cost-effectiveness studies. Therefore, we can conclude that is it still unclear whether LDI actually influences diagnostic and therapeutic decisions, patient outcomes and costs, and thus adds to the quality of care.

The aim of our study is to analyse the effectiveness and cost-effectiveness of LDI in burn care. The effect of the use of LDI in burn care on decision making, on clinical outcomes, on costs, and on cost effectiveness will be assessed. The current diagnostic strategy in burn depth assessment (clinical assessment) is compared with the new diagnostic strategy: LDI in combination with clinical assessment. We expect that LDI in combination with clinical assessment can lead to earlier excision and grafting in Dutch burn care. With the results of this cost-effectiveness study, we aim to provide a guidance to decide whether this instrument should be implemented in Dutch burn care.

## Methods/design

### Study design

A multicenter, randomised controlled trial will be conducted in the three Dutch burn centres: Beverwijk, Groningen and Rotterdam.

### Participants

All consecutive patients of any ages with acute burns of indeterminate depth (assessed by the treating clinician), who are seen within 5 days post burn at one of the three burn centres, are eligible.

Inclusion criteria:

• Patients with acute burns of indeterminate depth (=intermediate depth; the burn wound is not obviously superficial or obviously full thickness)

• Outpatient treatment or admission in one of the three Dutch burn centres

• Presentation within 5 days post burn

Exclusion criteria:

• The presence of full thickness wounds, next to intermediate wounds

• Topical treatment/dressings that impair scanning (e.g. hydrocolloid dressings)

• Patients with peri-orbital facial burns, in which the eyes are unable to shield

• Patients or their next of kin if they are under aged or temporary incompetent who can not be expected to give informed consent e.g. because of cognitive dysfunction or poor Dutch proficiency.

• Patients with a TBSA burned > 20%

### Intervention

We will include a total of 200 patients and randomly divide them in two groups: new diagnostic strategy versus current diagnostic strategy. In the first few days the burns will be treated with regular topical antimicrobials or dressings. LDI is performed between 48 hours and 5 days post burn in this study. After removal of the topical agent (during regular wound care), all wounds of indeterminate depth are scanned by a trained research physician or nurse, who is not involved in the patient treatment. In case of clearly superficial wounds next to intermediate wounds in a study patient, the superficial wounds will not be scanned; similar to what would happen in daily practice.

Results of LDI are (Figure 1): [12]

• Red/pink represents a healing potential within 14 days post burn

• Yellow/green represents a healing potential between 14–21 days

• Blue represents a healing potential > 21 days

### Outcomes

#### Primary outcome measure: wound healing time

Wound healing time is defined as the number of days between LDI (randomisation) and the day on which reepithelialisation of >95% is achieved. Next to that, for generalisation and LDI accuracy checks, we will present the time to wound healing from the day of injury. During wound care an experienced burn specialist will assess reepithelialisation; this is a reliable and valid technique (compared to digital image analysis) [16]. Wounds in admitted patients are assessed daily and wounds in outpatients two or three times a week. Differences in wound healing time between the two randomisation groups will be analysed.

#### Secondary outcomes measures

##### Quality of life and scar quality

Quality of life will be measured as soon as possible after injury to determine pre-injury functioning (at least within one month post burn) and after 3 months with the EuroQol-6D (EuroQol-5D + cognitive functioning; validated in patients aged ≥ 5 years) or the ItQol-47 questionnaire (validated in children < 5 years of age) [17-19].

The EuroQol-5D questionnaire can result in 243 different health states, which can be converted in a summary (utility) score between 0 (death) and 1 (perfect health) [18]. The EuroQol (EQ-5D) is an extensively used general health questionnaire to measure quality of life. It is recommended for the assessment of HRQoL in injury patients, especially for economic assessments [20].

Scar quality will be measured 3 months post-injury. Scar quality will be measured as follows;

• Elasticity will be measured with the Cutometer® Skin Elasticity Meter 575 (Courage and Khazaka Electronic GmbH, Cologne, Germany) The cutometer provides several elasticity parameters. In this study, maximal skin extension (Uf) (in mm) will be used, because this has been demonstrated to be the most reliable parameter [21].

• Vascularity and pigmentation will be measured with the Dermaspectometer, which is a reliable narrowband spectrometer that computes an erythema and melanin index (Cortex Technology, Hadshund, Denmark) [22].

• Subjective scar assessment will be performed by means of the Patients Observer Scar Assessment Scale (POSAS), a reliable and valid scar assessment tool that consists of a patient and observer scale [22,23]. The patient scores the scar characteristics colour, pliability, thickness, relief, itching and pain. The observer scale contains the items vascularisation, pliability, pigmentation, thickness, and relief. All items are scored numerically on a 10-point rating scale. In addition, the two observers and the patient give a general opinion on the scare quality on a 10-point rating scale.

Differences in quality of life and scar quality 3 months post burn between the two diagnostic groups will be analysed.

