### Sample size

A total of 57.5% of admitted burn patients in the Netherlands is treated conservatively (unpublished data, Dutch Burn Repository R3, 2011). The time to wound healing in patients without surgery is approximately 13 days, this will not change after the introduction of LDI. In the 42.5% of surgically treated patients we do expect an effect on wound healing time, because of an earlier operation. The mean time to first transplantation is 14.0 days post burn, the mean time to wound healing is 5 days after surgery [28], resulting in a mean time to wound healing of 19.0 days. The overall mean time to wound healing for all patients combined is 15.6 days ((57.5%*13+ 42.5%*19)/100).

Petrie et al. describe a reduction of 5.3 days in LOS in patients undergoing surgery, after the introduction of the LDI. As a result, in our population, an overall effect of 2.25 (57.5%* 5.3) days can be expected, with a standard deviation of 5 days. A 2-sided test with an α level of 0.05 and a β level of 0.20 (power 0.80) indicates a required total sample size of 190 patients. We expect a low drop out rate because of a short time to follow up to assess primary outcome (time to wound healing). With a 5% drop out we need a total sample size of 200.

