## Randomisation

Patients are randomly allocated to the group ‘new diagnostic strategy’ or the group ‘current diagnostic strategy’, on the day of the LDI scan. Stratification will be performed for the three different centers and the severity of the burns: total burned surface area ≤10% or >10%. A randomisation list is prepared for each stratum on the principle of random permuted blocks of patients, using a random number table [29]. The allocation sequence is concealed by using sequentially numbered, opaque sealed envelopes (SNOSE) prepared by the coordinating researcher ([name]) which are opened at day of LDI after having obtained informed consent, by one of the local researchers [30].

The care provider, outcome assessor and patients are blinded to the results of the LDI in the group ‘current diagnostic strategy’. However, they are not blinded to the group in which patients are randomised.

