## Statistical analysis

Data will be primarily analysed according to the intention-to-treat principle. We assume that time to LDI will be equal in both diagnostic groups, as a result of randomisation. Thus, the differences in effects (e.g. time to wound healing) and costs will be assessed from randomisation onwards.

Differences in time to wound healing (numbers of days between LDI and day of > 95% reepithelialisation) and timing of surgery in both diagnostic strategy groups will be analysed with Kaplan-Meier curves and log rank test.

Quality of life (derived from the ItQol-47 and EuroQol-6D), scar quality (assessed by the Cutometer®, Dermaspectometer® and POSAS) and length of hospital stay will be analysed using the independent-sample-t-test (in case of normal distribution) or the Mann–Whitney test (non-normal distribution).

Differences in diagnostic and therapeutic decisions will be analysed with the Chi-square test. Diagnostic accuracy will be assessed by calculating sensitivity and specificity of the LDI compared to the reference test: time to wound healing (in conservative treated patients) or biopsy (in surgical treated patients). In addition, receiver operating characteristic (ROC) curves will be calculated for both diagnostic groups.

Differences in mean costs (after randomisation) will be analysed by the Mann–Whitney test, since healthcare costs are typically highly skewed. Non-parametric techniques (bootstrapping) will be used to derive a 95% confidence interval for the differences in distributions of the costs.

The cost-effectiveness analysis and cost-utility analysis are performed by dividing the differences in average costs by the differences in average effects or utility. In a sensitivity analysis, the impact on cost-effectiveness of statistical uncertainty on the main study outcomes will be determined (uni- and multivariable).

Data analysis will be performed using SPSS-software (Statistical Package for the Social Sciences).

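### The recalled pre-injury quality-of-life score has no role in the 3-month comparison, which costs precision, and may be taken after allocation is known, which makes it a less clean covariate

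*Protocol article*

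**What the plan says.** All places are in the protocol article.

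- **Quality of life and scar quality** sets the first measurement: "Quality of life will be measured as soon as possible after injury to determine pre-injury functioning (at least within one month post burn"). I read the bracket as an outer limit of one month. The same questionnaire is repeated after 3 months: EuroQol-6D from age 5, ItQol-47 below that age. The planned comparison is at the later time only: "Differences in quality of life and scar quality 3 months post burn between the two diagnostic groups will be analysed".
- **Statistical analysis** names the method. Quality of life, together with scar quality and length of stay, "will be analysed using the independent-sample-t-test (in case of normal distribution) or the Mann–Whitney test (non-normal distribution"). No baseline term appears.
- **Randomisation** places allocation "on the day of the LDI scan", by opening an envelope once consent has been obtained. On knowledge of the arm by care providers, assessors and patients it says: "However, they are not blinded to the group in which patients are randomised". Only the scan result is withheld, and only in the current-strategy group.
- **Intervention** fixes the scan day: "LDI is performed between 48 hours and 5 days post burn in this study".
- **Economic evaluation** forms QALYs from utility and time spent in each health state, for patients aged 5 and over. It does not say whether the pre-injury score enters.

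**The concern.** There are two linked weaknesses.

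First, the trial pays for a pre-injury score on the same scale as the outcome and then does not use it in the comparison it states. Patients of any age are eligible. To the extent that pre-injury score predicts 3-month score, its spread stays in the error term. Each quality-of-life comparison also rests on fewer than the full 200 patients, because the instrument changes at age 5.

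Second, the obvious remedy is not clean as the schedule stands. Nothing places the questionnaire before allocation. A score given two or three weeks after the envelope was opened comes from a patient, or parent, who knows the arm and has lived through some of its consequences. Adjusting for such a score means adjusting for something the arm may have touched. The same would apply to QALYs that used it as a starting value.

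At stake is the precision of a secondary outcome and the usability of its only baseline. The wound-healing analysis is not involved. Nor are the scar measures, which have no pre-injury counterpart.

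**Working it through.** **Timing.** Inputs: outer limit one month post burn, taken as 30 days; randomisation on day 2 to 5.

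- Part of the window that can follow allocation: 30 − 5 = 25 to 30 − 2 = 28 days.
- The Sample size section gives the healing times. Without surgery: "The time to wound healing in patients without surgery is approximately 13 days". With surgery, 14.0 + 5 days, "resulting in a mean time to wound healing of 19.0 days". Its overall mean reproduces: 0.575 × 13 + 0.425 × 19 = 7.475 + 8.075 = 15.55, printed as 15.6.
- From these means to the end of the window: 30 − 13 = 17, 30 − 15.6 = 14.4 and 30 − 19 = 11 days.

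A permitted baseline *can* therefore fall after allocation and after healing. How often it does cannot be worked out, because the distribution of completion days is not given.

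**Precision.** The article gives no standard deviation, correlation or power for quality of life, so there is no planned figure to reproduce. Let r be the correlation between pre-injury and 3-month score (an assumption). With the baseline as a covariate:

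- variance of the difference = (1 − r²) × unadjusted variance
- reduction in standard error = 1 − √(1 − r²)
- equivalent sample size = N / (1 − r²)

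For illustration, take the article's 190 evaluable patients, 95 per arm, on one instrument. The standardised difference detectable without adjustment (two-sided 5%, power 80%) is (1.960 + 0.842) × √(2/95) = 0.406. With adjustment it is 0.406 × √(1 − r²).

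| r (assumed) | 1 − r² | Variance removed | SE smaller by | 190 patients worth | Detectable difference (SD) |
|---|---|---|---|---|---|
| 0.2 | 0.96 | 4% | 2.0% | 198 | 0.398 |
| 0.3 | 0.91 | 9% | 4.6% | 209 | 0.388 |
| 0.5 | 0.75 | 25% | 13.4% | 253 | 0.352 |
| 0.6 | 0.64 | 36% | 20.0% | 297 | 0.325 |

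The last two columns overstate what can be had, since each instrument covers only part of the 190. The formula belongs to the linear model and does not carry over directly to the Mann–Whitney branch.

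**Effect of a contaminated baseline.** The planned test does not contain the score, so a shift in it by arm changes nothing there. In an adjusted model, the estimate is the outcome difference minus slope × baseline difference. With equal variances the slope is r. A purely arm-caused shift of b SD in the recalled score then moves the adjusted estimate by −r × b. For example, r = 0.5 and b = 0.1 give −0.05 SD. The documents give no value for b, so this shows the mechanism only.

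**The case against.** The strongest reply is that an unadjusted test between randomised groups is valid and its standard error already allows for chance imbalance. Adjustment is then a refinement, and if late scores are suspect, leaving them out is the safe choice. The first part stands: the stated analysis is not wrong. The second part stands for the present schedule, which is why the timing should change along with the model. Since the window and the test are both stated, this is a choice that can be improved and not a detail left to another document.

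It can also be said that the questionnaire asks about the state before the burn, so it is retrospective even on day 2, and that healing or surgery does not alter what is asked. That stands too. The arm can act only through recall or response shift, which is possible but cannot be sized here. A recalled score may also correlate only weakly with the 3-month score.

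A reader might go further in three ways that the article does not support:

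- *That baselines are often taken after healing.* The operative rule is as soon as possible; a month is the limit, and 25 to 28 days after randomisation is the latest case.
- *That the 3-month comparison is biased.* A score that is not used cannot bias it.
- *That a null quality-of-life result by itself moves the economic evaluation to cost-minimisation.* The Economic evaluation section requires no difference in wound healing as well, and its main ratio uses healing time.

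**Conclusion.** The point holds as one of efficiency and of baseline timing. A pre-injury score on the same instrument is collected and left out of a valid but less precise comparison. Because it may be recorded up to 25 to 28 days after allocation is known, it is a less clean covariate than it could be, and a less clean QALY input if it is used for that.

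The gain from a well-timed, adjusted analysis is 4% to 36% of the variance for r from 0.2 to 0.6. It is minor at r of 0.3 or below and worthwhile from about 0.5. This rests on an assumed correlation and on a linear model. Possible distortion of late scores is a reason for caution, not a demonstrated effect. The change is worth making because it is cheap, but no planned inference is invalid without it and the primary analysis is unaffected.

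**What to change.** 1. **Quality of life and scar quality:** have the pre-injury questionnaire (EuroQol-6D or ItQol-47, by a parent where needed) completed after consent and before the envelope is opened where possible, and record the completion date for every patient.
2. **Statistical analysis:** for quality of life, replace the two-sample test by a linear regression of the 3-month score on arm and pre-injury score, separately for each instrument, with robust or bootstrap confidence intervals if the scores are skewed.
3. **Sensitivity analysis:** treat baselines dated after allocation as missing, and report the unadjusted comparison alongside.
4. **Economic evaluation:** say whether the pre-injury score enters the QALYs; if it does, apply the same check there.

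The cost is a few minutes on the scan day, when a local researcher is already involved, and some added analysis wording. No extra visit or patient is needed. The Discussion says that inclusion began in December 2011, so patients already enrolled keep whatever later baseline they have. For them only the date, if known, and the sensitivity analysis can help, and treating late scores as missing gives back part of the precision gained.
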